## Abstract

**Background:**

Acute chest pain is a major health problem all over the western world. Active approaches are directed towards diagnosis and treatment of potentially life threatening conditions, especially acute coronary syndrome/ischemic heart disease. However, according to the literature, chest pain may also be due to a variety of extra-cardiac disorders including dysfunction of muscles and joints of the chest wall or the cervical and thoracic part of the spine. The diagnostic approaches and treatment options for this group of patients are scarce and formal clinical studies addressing the effect of various treatments are lacking.

**Methods/Design:**

We present an ongoing trial on the potential usefulness of chiropractic diagnosis and treatment in patients dismissed from an acute chest pain clinic without a diagnosis of acute coronary syndrome. The aims are to determine the proportion of patients in whom chest pain may be of musculoskeletal rather than cardiac origin and to investigate the decision process of a chiropractor in diagnosing these patients; further, to examine whether chiropractic treatment can reduce pain and improve physical function when compared to advice directed towards promoting self-management, and, finally, to estimate the cost-effectiveness of these procedures. This study will include 300 patients discharged from a university hospital acute chest pain clinic without a diagnosis of acute coronary syndrome or any other obvious cardiac or non-cardiac disease. After completion of the clinic's standard cardiovascular diagnostic procedures, trial patients will be examined according to a standardized protocol including a) a self-report questionnaire; b) a semi-structured interview; c) a general health examination; and d) a specific manual examination of the muscles and joints of the neck, thoracic spine, and thorax in order to determine whether the pain is likely to be of musculoskeletal origin. To describe the patients status with regards to ischemic heart disease, and to compare and indirectly validate the musculoskeletal diagnosis, myocardial perfusion scintigraphy is performed in all patients 2–4 weeks following discharge. Descriptive statistics including parametric and non-parametric methods will be applied in order to compare patients with and without musculoskeletal chest pain in relation to their scintigraphic findings. The decision making process of the chiropractor will be elucidated and reconstructed using the CART method. Out of the 300 patients 120 intended patients with suspected musculoskeletal chest pain will be randomized into one of two groups: a) a course of chiropractic treatment (therapy group) of up to ten treatment sessions focusing on high velocity, low amplitude manipulation of the cervical and thoracic spine, mobilisation, and soft tissue techniques. b) Advice promoting self-management and individual instructions focusing on posture and muscle stretch (advice group). Outcome measures are pain, physical function, overall health, self-perceived treatment effect, and cost-effectiveness.

**Discussion:**

This study may potentially demonstrate that a chiropractor is able to identify a subset of patients suffering from chest pain predominantly of musculoskeletal origin among patients discharged from an acute chest pain clinic with no apparent cardiac condition. Furthermore knowledge about the benefits of manual treatment of patients with musculoskeletal chest pain will inform clinical decision and policy development in relation to clinical practice.

**Trial registration:**

NCT00462241 and NCT00373828

## Background

Acute chest pain is believed to be one of the most common reasons for hospital admission in Denmark [1,2]. Figures from the United States show that chest pain is the second most common reason for emergency department visits, accounting for 5.4% or more than 4 million visits per year [3]. The primary concern in these cases is of cause cardiac disease, but in about 50% of cases the aetiology appear to be non-cardiac [4,5], and in around 20% of the patients admitted to chest pain clinics no definitive diagnosis can be made [6].

Chest pain patients with normal coronary perfusion have an excellent prognosis for survival, and a future risk of cardiac morbidity similar to that reported in the background population [7-9]. However, about three quarters of patients with undiagnosed chest pain continue to suffer from residual pain with large personal and socio-economic consequences in terms of anxiety, fear of undiagnosed heart disease, loss of daily function and working capacity, and re-admissions to the hospital [10-16]. Chest pain differential diagnoses include primarily pulmonary, gastrointestinal, psychosocial, or musculoskeletal problems. Musculoskeletal problems alone accounts for 5–20% of the total number of admissions in acute chest pain clinics [16-18]. Hence, the musculoskeletal system is a recognized possible source of pain in patients with chest pain, even if no standardized criteria for the diagnosis exist at this point.

An extensive body of literature addresses patient assessment and management protocols for patients presenting with chest pain, but these focus primarily on cardiopulmonary [19-22], gastro-oesophageal [5,23], and psychological conditions [11,24,25], and protocols aiming at diagnosis of musculoskeletal chest pain remain scarce, and the effect of treatment strategies, including medical treatment (oral anti-inflammatory drugs), exercise (strength and/or stretching), advice, and manual approaches have not been evaluated. To our knowledge, only one non-randomized study deals with manual examination and treatment of patients with musculoskeletal chest pain [26,27]. In this study, an examination program consisting of a general health examination and a specific manual examination of the thorax and cervico-thoracic part of the spine was developed for a population of patients with suspected or known stable angina pectoris referred to a tertiary hospital for coronary angiography [26]. The examination program together with the detailed case history was applied by a chiropractor to make a diagnosis of discomfort from the musculoskeletal system, cervico-thoracic angina (CTA). In the absence of a true golden standard to validate the CTA diagnosis, myocardial perfusion scintigraphy (MPS) was used as a *by proxy *measure of validity with some success: Eighty percent of the CTA-positive patients had normal perfusion compared to 50% in the CTA-negative group. Moreover, results indicated that patients with CTA may benefit from chiropractic treatment.

We therefore decided to perform a multi-purpose clinical trial consisting of 1) a prospective, population-based, diagnostic evaluation study, 2) a single-blinded, randomized clinical trial (RCT), and 3) a cost-effectiveness analysis alongside the RCT.

The aims are:

• To determine the proportion of patients discharged from a university hospital chest pain clinic in whom their chest pain may be of musculoskeletal rather than cardiac origin. Specifically, we wish to determine the prevalence and character of musculoskeletal chest pain, and to describe cardiac status with respect to ischemic heart disease.

• To investigate the diagnostic decision making process of a chiropractor in these patients, using MPS as an indirect measure of validity.

• To determine the relative clinical effectiveness of chiropractic manual treatment versus advice directed towards promoting self-management using pain and patient-rated outcomes as primary outcome measures. Finally, we will estimate the cost-effectiveness of these procedures.

## Methods/Design

This clinical trial is being conducted at Odense University Hospital in Odense, Denmark. The study began in 2006, and is ongoing. Approval has been granted by the regional ethics committee for Funen and Vejle Counties, Denmark, approval number #VF 20060002, and informed consent is obtained from all participants.

### Study population

Three hundred consecutive patients with an episode of suspected non-cardiac acute chest pain are being recruited among patients discharged from an acute chest pain clinic situated at a large specialized cardiology department. All patients have undergone a standardized evaluation program at the chest pain clinic ruling out any obvious and significant cardiac or non-cardiac disease, including acute coronary syndrome. Following discharge from the chest pain clinic, all patient records are screened for the inclusion and exclusion criteria into the present study, and potential participants are contacted personally or by telephone and invited to participate.

### Inclusion/exclusion criteria

The inclusion and exclusion criteria are presented in Table 1.

**Table 1 T1:** Inclusion and exclusion criteria.

**Inclusion criteria**	**Exclusion criteria**
*To be included in the project the participant must*	*Patients will not be included if any of the following conditions are present*
- Have chest pain as their primary complaint.	- Acute coronary syndrome.
- Have an acute episode of pain of less than 7 days duration before admission.	- Previous Percutaneous Coronary Intervention or Coronary Artery By-pass Grafting.
- Consent to the standardized evaluation program at the chest pain clinic.	- Chest pain from other definite cause, cardiac or non-cardiac. The condition must be verified clinically during admission (i.e. pulmonary embolism, pneumonia, dissection of the aorta, ...).
- Have pain in the thorax and/or neck.	- Inflammatory joint disease.
- Be able to read and understand Danish.	- Insulin dependent diabetes
- Be between 18 and 75 year of age.	- Fibromyalgia.
- Be a resident of the Funen County	- Malignant disease.
	- Apoplexy, dementia, or unable to cooperate.
	- Major osseous anomaly.
	- Osteoporosis.
	- Pregnancy.
	- Does not want to participate.
	- Other – the reason for non-inclusion will be registered.

A record will be kept of the number of subjects excluded from the study, as well as those who are eligible for inclusion and choose not to participate.

### Baseline measurements

Interested individuals are assessed at baseline within seven days of admission. First, they complete a questionnaire including information on pain, general health, occupation, education, physical and lifestyle factors, expectation to treatment outcome, and baseline values for the outcome measures.

Next, participants are examined using a standardized and previously validated study protocol [26]. The examination protocol consists of three parts:

*1) A semi-structured interview *including pain characteristics (frequency, duration, localization, provoking and relieving factors), symptoms from the lungs and gastrointestinal system, past medical history, height and weight, and risk factors for ischemic heart disease. Further, patients are classified into three types of chest pain: typical angina, atypical angina, or non-cardiac chest pain in accordance with Danish and international guidelines [19,21]. The patients are also classified into one of four classes of severity according to the criteria given by the Canadian Cardiovascular Society (CCS) [21,28]. Cardio-vascular performance is graded according to New York Heart Association (NYHA) [29].

*2) A general health examination *including blood pressure and pulse, heart and lung stethoscopy, abdominal palpation, neck auscultation, clinical signs of left ventricular failure, neurological examination of the upper and lower extremities in terms of reflexes, sensibility to touch, muscle strength, and an orthopaedic examination of the neck and shoulder joints in order to rule out nerve root compression syndromes.

*3) A specific manual examination *of the muscles and joints of the neck, thoracic spine and thorax, including active range of motion, manual palpation for muscular tenderness on 14 points of the anterior chest wall, palpation for segmental paraspinal muscular tenderness, motion palpation for joint-play restriction of the thoracic spine (Th1–8), and end play restriction of the cervical and thoracic spine [26].

The examination program together with the detailed case history will be applied by a chiropractor to make a diagnosis of pain from the musculoskeletal system, CTA, according to the previously established criteria [26].

The timeline and overview of data collection is shown in Figure 1 (adapted from Perera et al. (2007)[30]). The timeline is shown vertically, and allocation of participants to study groups horizontally.

**Figure 1 F1:**
[figure not shown]
Evaluation, intervention and follow up. (Adapted from Perera et al. 2007).

### MPS

In order to evaluate the population in terms of ischemic heart disease all patients undergo MPS within two to four weeks following baseline evaluation. Using radionuclides the myocardial perfusion is evaluated to determine the presence of regional areas with decreased blood flow because of coronary artery disease. Detailed procedures for MPS are described in Appendix 1. MPS will also be used to compare and indirectly validate the musculoskeletal diagnosis.

### RCT

All CTA positive patients (estimated 120 out of the initial 300 patients) will be included in the RCT. The aim of this part of the study is to establish the effectiveness of chiropractic treatment including spinal manipulation versus advice to promote self-management. Participants are only eligible for inclusion in the RCT if they are CTA positive and the examining clinician decides that manipulation might be the appropriate treatment. Patients for whom manipulation is thought not to be indicated will not be included in the RCT.

### Randomization

The randomization sequence with a 1:1 allocation ratio has been computer generated by a researcher not involved in the project. Consecutively numbered sealed opaque envelopes containing the treatment allocation for each patient has been produced and eligible participants draw an envelope. The envelopes are arranged in blocks with varying block sizes. The examining clinician manages the hand over of the envelope to the participant, but is masked to the treatment allocation when determining eligibility to randomization.

### Treatments

Participants will be randomized to receive one of two treatments: A course of chiropractic treatment including spinal manipulation (therapy group) or advice promoting self-management (advice group).

#### Therapy group

Participants in the therapy group will be assigned to a chiropractor in their local community. Participating chiropractors will have a university chiropractic degree and at least five years of clinical experience. Each chiropractor chooses an individual treatment strategy based on a combination of their findings, the patient history, and pragmatic, routine practice. The treatment will be modified to accommodate the age and physical condition of each patient. The treatment must, however, include high velocity, low amplitude manipulation directed towards the thoracic and/or cervical spine in combination with any of the following: Joint mobilisation, soft tissue techniques, stretching, stabilising or strengthening exercises, heat or cold treatment, and advice. The protocol specifies up to ten treatment sessions of approximately 20 minutes, 1–3 times per week for four weeks, or until the patient is pain free if this occurs within less than four weeks. The type of manipulation technique will not be standardized, and the treating chiropractor can manipulate the lumbar spine if he/she determines to do so. The chiropractors record the types of treatment rendered at all sessions.

#### Advice group

Advice is given in an approximately 15-minute session following the baseline assessment, and is directed towards promoting self-management. The participants are told that their chest pain generally has a benign, self-limiting course. The participants receive individual instructions regarding posture and two or three exercises aiming to increase spinal or muscle stretch based on clinical evaluation. They are advised to seek medical attention for re-evaluation (family physician, chest pain clinic or emergency department) in case of severe or unfamiliar chest pain. Further, the advice group is asked to refrain from seeking any manual treatment for the following four weeks.

### Outcome measures

The outcomes are measures by self-report questionnaires that are collected at baseline, after four weeks (CTA positive patients only), and after three and 12 months (all patients) (see Figure 1).

#### Primary outcome measures in the RCT

Participants are asked to rate their worst level of chest pain during the last week, using an ordinal 11-point box scale (0 = no pain, 10 = the worst pain possible). Improvement in chest pain is rated by participants on a 7-point ordinal scale with responses ranging from "much worse" to "much better".

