#### Secondary outcome measures

• Ordinal 11-point box scales (0 = no pain, 10 = the worst pain possible) will be used to rate chest pain "now" (i.e. on the day of examination/completion of questionnaire) together with the following types of pain over the last week: "worst" and "average" chest pain, "average" thoracic spine pain, "average" cervical spine pain, "average" shoulder and arm pain.

• Improvement in chest pain and general health is rated by the participants using an ordinal 7-point scale using the categories: "Much worse", "worse", "a little worse", "no change", "a little better", "better", and "much better".

• The general health status is measures by the Medical Outcomes Study Short Form 36-item Health Survey (SF-36) [31,32]. The SF-36 comprises 36 items that can be combined into eight multi-item summary scores: physical functioning, vitality, bodily pain, mental health, social functioning, role limitation due to physical health and due to emotional problems, and general health perception, plus one item assessing a change in health over the past year.

• The Patient Specific Functional Scale is developed to assess functional limitations in a variety of clinical presentations [33]. Participants will be asked to identify three important activities with which they are having difficulties or are unable to perform because of their problem. In addition to specifying the activities the participants will be asked to rate on an ordinal 11-point box scale the current level of difficulty associated with each activity.

• As a surrogate for the assessment of pain and quality of life, we will use the indicators "number of visits to family doctor", "number of hospitalizations", and "amount of prescribed drugs". The data will be obtained from the comprehensive national Danish central registers. Non-prescription medication use for chest pain is measured using self-report questionnaires at 12 and 52 weeks.

• Information about adverse events and side effects will be collected for the therapy group by the treating chiropractor before and after each treatment session.

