### Outcome measures

We have chosen global perceived effect as one out of two primary outcome measures even though critique has been posted on the reliability and validity of global rating scales [39]. Global rating scales are typically correlated with the patients' present status and are not an unbiased measure of change. However, global rating scales are regarded as clinically relevant and valid, and responsive to measure patients' perceived recovery. The global rating scale was also chosen, because during the pilot study we found that pain intensity levels were relatively low compared to for instance patients seeking care for low back pain. Patients initially reported very high levels of pain which then spontaneous decline in intensity within a very short period of time (hours to days), rendering pain a less than optimal primary outcome measure. Finally, we found that the Patient Specific Functional Scale [33] would not make a good primary outcome measure because many patients experience a first time episode of chest pain and, thus, do not feel limited in their daily activities.

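### Baseline worst pain in the last week always covers the admission day, so the planned change score may subtract a fading acute episode and lose precision on the pain primary

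*Protocol article*

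**What the plan says.** All references are to the Protocol article.

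- **Pain primary** (section on the RCT's primary outcomes): "Participants are asked to rate their worst level of chest pain during the last week, using an ordinal 11-point box scale".
- **Timing of baseline** (Baseline measurements): "Interested individuals are assessed at baseline within seven days of admission". The questionnaire completed then includes "baseline values for the outcome measures".
- **Index episode** (Table 1): the patient must "Have an acute episode of pain of less than 7 days duration before admission".
- **Course of the pain** (Discussion, Outcome measures): "Patients initially reported very high levels of pain which then spontaneous decline in intensity within a very short period of time (hours to days"), which the protocol describes as "rendering pain a less than optimal primary outcome measure". It gives this as one reason for making a global rating of improvement the other primary, but keeps worst pain in the last week.
- **Current pain** (Secondary outcome measures): the box scales "will be used to rate chest pain 'now' (i.e. on the day of examination/completion of questionnaire"). This score is secondary only.
- **Entry to the RCT** (RCT): a positive CTA diagnosis and the clinician's judgement that manipulation might be appropriate. No level of current pain is stated.
- **Analysis** (Data analyses, Randomized controlled trial): differences between baseline and follow-up are calculated and compared, with adjustment for baseline by ANCOVA only if needed.

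**The concern.** The recall period of the pain item and the time allowed for baseline are both seven days. The item asks for the worst pain, so pain on the admission day sets a lower limit on the baseline score even in a patient who has since largely recovered. Follow-up at four weeks, three months and 12 months uses the same item over weeks that do not contain the admission. The item may thus capture an acute episode at baseline and later pain at follow-up.

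A baseline of that kind may predict follow-up poorly. Subtracting a weak predictor adds noise to the outcome, and adjusting for it gains little. The fall in both arms would also contain spontaneous resolution that the baseline score cannot separate from change in pain still present when treatment began.

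**Working it through.** **1. The stated power.** The only power figure in the plan is 81% with 120 patients, for a shift in the improvement scale from 0/5/25/45/25% to 1/10/40/40/9%. With 60 per arm, a Wilcoxon test and two-sided 5% (assumed, as alpha is not stated), simulation gives 81.3%. The figure reproduces, but it concerns the improvement rating, which has no baseline score. It gives no information about the pain primary.

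**2. Does the window always include admission?** Let admission be day 0 and baseline day t, with t from 0 to 7. The recall window runs from t − 7 to t, and t − 7 ≤ 0 for every allowed t.

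| Baseline day t | Window | Days before admission covered |
|---|---|---|
| 0 | −7 to 0 | 7 |
| 3 | −4 to 3 | 4 |
| 7 | 0 to 7 | 0 |

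The admission day is always inside, at t = 7 only just. Pain may begin up to a week before admission, so a peak before admission can fall outside a late window. The baseline score therefore also depends on how soon after admission it was taken. The four-week window begins about 28 − 7 = 21 days after baseline, clear of the admission week.

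**3. What the change score costs.** The score is treated as numeric, as the plan does when it takes differences. Assume equal variance σ² at baseline and follow-up, with correlation r. Variances per patient are:

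- follow-up alone: σ²
- change score: 2σ²(1 − r)
- ANCOVA: σ²(1 − r²)

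Change is noisier than follow-up alone when 2(1 − r) > 1, that is, when r < 0.5. The ratio of change to ANCOVA is 2(1 − r)/(1 − r²) = 2/(1 + r).

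| r (assumed) | Follow-up alone | Change | ANCOVA | Change ÷ ANCOVA |
|---|---|---|---|---|
| 0 | 1 | 2.00 | 1.00 | 2.00 |
| 0.2 | 1 | 1.60 | 0.96 | 1.67 |
| 0.5 | 1 | 1.00 | 0.75 | 1.33 |
| 0.7 | 1 | 0.60 | 0.51 | 1.18 |

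At r = 0.2, a confidence interval from the change score is √1.67 ≈ 1.29 times as wide as one from ANCOVA. Put as sample size, ANCOVA with 120 × 0.96/1.60 = 72 patients would match the change score with 120. At every r below 1, ANCOVA has the smaller variance.

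**4. Is a low r plausible?** The documents give no value. A baseline dominated by pain that falls within hours to days makes a low r plausible, but does not establish it.

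**The case against.** **The weakness of pain as an outcome is disclosed.** The Discussion calls it less than optimal and adds the global rating partly for that reason. A 36-patient pilot informed the primary outcomes, and the pain scales were adjusted afterwards. This stands, but the text does not mention that the recall window overlaps the admission, nor does it change the baseline comparison.

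**There is no bias.** Both arms carry the same kind of baseline, allocation is random and analysis is by intention to treat. This stands in full. A reader might infer that the fall within the therapy arm will be presented as a treatment effect, but no section plans a within-arm reading.

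**Recovered patients diluting the effect.** A reader might infer that many randomised patients are already pain-free, cannot benefit, and so erode power. If 10%, 20% or 30% of the therapy arm followed the control distribution, the 81% would fall to about 72%, 61% or 50%. The documents do not support using these figures here. The share is unknown, and the calculation concerns the improvement scale, which the recall window does not touch. The Discussion says that pain declines in intensity, not that it vanishes. The Background reports residual pain in about three quarters of patients with undiagnosed chest pain. Entry also passes through a clinical judgement, and later pain up to 12 months is part of the target.

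**Replacing the baseline item with 'now' would be worse.** A change score would then subtract one item from a different one. This is right, and it is why 'now' is proposed only as an added covariate.

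**Such details belong in an analysis plan that is not shown.** This is fair for the supportive analysis. The change-from-baseline comparison with optional adjustment, however, is fixed in the protocol itself.

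**Conclusion.** The point holds as one of precision and interpretation. Every baseline worst-pain score covers the admission day and may reflect an episode that the protocol itself describes as short-lived. The planned comparison subtracts that score. The treatment contrast remains unbiased.

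The size of the loss depends on a correlation that the documents do not give. With equal variances, the change score is worse than ignoring baseline altogether if r is below 0.5. At r = 0.2 it carries 1.6 times the variance of follow-up alone and about 1.67 times that of ANCOVA. If r is above 0.5 the change score beats follow-up alone but still loses to ANCOVA, so the case for ANCOVA does not rest on a particular r. The documents do not establish how many patients have recovered by baseline, and no loss of power on the improvement rating is claimed.

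**What to change.** 1. Make the primary analysis of the pain outcome an ANCOVA of follow-up worst pain in the last week, in place of the change score and of adjustment only if needed. Include baseline worst pain and baseline chest pain 'now' as covariates.
2. Pre-specify a supportive analysis of both primaries by baseline 'now' pain (0 versus above 0). Keep the analysis of all randomised patients primary.

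Keep the worst-pain item as it is at baseline and follow-up, and do not put 'now' into a change score.

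The cost is wording in the analysis section. The 'now' score is among the outcomes whose baseline values the questionnaire collects, so no new item, visit or patient is needed. Intervals within the subsets will be wider, and a single-day score of 0 can miss intermittent pain, so the split should be read as supportive only. How much precision the 'now' covariate adds beyond baseline worst pain cannot be computed from the documents.

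### The RCT has two unranked primary outcomes at three follow-ups and no named primary visit, while its 81% power is that of a single test of one outcome

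*Protocol article*

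**What the plan says.** - **Aims (Background).** Treatment effectiveness is to be judged "using pain and patient-rated outcomes as primary outcome measures". No visit is given.
- **Primary outcome measures in the RCT.** Two outcomes are listed. The first is on a 0-10 box scale: "Participants are asked to rate their worst level of chest pain during the last week". The second is a global rating: "Improvement in chest pain is rated by participants on a 7-point ordinal scale".
- **Outcome measures (Discussion).** The count is confirmed: "We have chosen global perceived effect as one out of two primary outcome measures". The section adds that pain falls quickly by itself, "rendering pain a less than optimal primary outcome measure".
- **Outcome measures (Methods).** Questionnaires are "collected at baseline, after four weeks (CTA positive patients only), and after three and 12 months (all patients". Everyone in the RCT is CTA positive, so all three follow-ups apply to them.
- **Secondary outcome measures.** Worst chest pain over the last week and improvement in chest pain both appear again, with no different visit attached.
- **Randomized controlled trial (Data analyses).** 120 patients give 81% power for a shift in improvement from 0/5/25/45/25% to 1/10/40/40/9%. No alpha, sidedness or visit is stated, and worst pain is not powered. Changes from baseline to follow-up are to be computed and compared. A repeated-measures MANCOVA over the primary and secondary patient-rated outcomes serves as an overall test and is labelled secondary.
- **Advice group.** "the advice group is asked to refrain from seeking any manual treatment for the following four weeks".

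**The concern.** A primary outcome is fixed once the variable, the visit and the rule for success are fixed. Here two variables share the status, three visits are open, and no rule links them. That gives 2 × 3 = 6 comparisons, each of which could later be presented as the primary result without departing from the text.

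Two things are at stake. One is the false-positive risk if a favourable comparison is picked from the set. The other is the power statement: 81% for one test is not the power of a design with two primary outcomes once the error is controlled.

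The visits also answer different questions. Treatment and the advice arm's request to avoid manual care both cover four weeks. Week 4 therefore compares the arms while the request holds, and later contrasts may include manual treatment in the advice arm.

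**Working it through.** **Inputs from the article:** 120 patients, 1:1 allocation (60 per arm); improvement distributions 0/5/25/45/25% and 1/10/40/40/9%; two primary outcomes; three follow-ups. **Assumptions:** two-sided alpha 0.05, and the correlations used in step 4. The article gives neither.

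**1. Reproduce the stated power.** For a Wilcoxon test on ordered categories, the effect is P = P(X>Y) + ½P(tie), summed over the categories of the better distribution:

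- 0.05 × (0.01 + 0.05) = 0.0030
- 0.25 × (0.11 + 0.20) = 0.0775
- 0.45 × (0.51 + 0.20) = 0.3195
- 0.25 × (0.91 + 0.045) = 0.23875
- P = 0.63875

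The mean category proportions are 0.005, 0.075, 0.325, 0.425 and 0.17. Their cubes sum to 0.1164, so the tie factor is 1 − 0.1164 = 0.8836.

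Tie-corrected Noether formula: power = Φ(√(12 × 120 × 0.25 / 0.8836) × (P − 0.5) − z) = Φ(20.185 × 0.13875 − 1.960) = Φ(0.841) = 80.0%.

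Simulating the tie-corrected test gives 81.2%. The stated 81% is therefore reproduced as one two-sided 0.05 test of improvement. One-sided 0.05 would give about 88-90%, which does not match.

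**2. Two outcomes at one visit, Bonferroni (alpha 0.025).** Φ(2.801 − 2.241) = Φ(0.559) = 71.2%; simulation gives 72.4%. By the formula, about 150 patients would restore 81%.

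**3. Six comparisons, Bonferroni (alpha 0.05/6 = 0.0083).** Φ(2.801 − 2.638) = Φ(0.162) = 56.5%; simulation gives 57%. By the formula, about 190 patients would restore 81%.

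**4. Familywise error if each comparison is tested at 0.05 and any one counts.** With independence, six tests give 1 − 0.95⁶ = 26.5% and two give 1 − 0.95² = 9.75%. Repeated ratings of the same pain are positively correlated, so independence is a ceiling. The simulated values below use two structures: one correlation for every pair, or the same correlation between outcomes and between visits with their product for pairs that differ in both.

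| Assumed correlation | Six tests, one correlation | Six tests, product structure | Two tests |
|---|---|---|---|
| 0.3 | 24.2% | 24.9% | 9.5% |
| 0.5 | 20.7% | 21.9% | 9.0% |
| 0.7 | 16.4% | 17.6% | 8.3% |
| 0.9 | 10.9% | 11.6% | 7.1% |

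The range is about 11-25% for six comparisons and, with the independent case included, about 7-10% for two.

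**5. Does the MANCOVA supply control?** It would if it were the primary test, or if the individual comparisons were read only after it succeeded. The article says neither. It also includes the secondary outcomes, so a significant result would not show that a primary outcome differs.

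**The case against.** The best defence is that this is a condensed journal article. Multiplicity rules and alpha allocation commonly sit in an analysis plan that is not shown, and the figure with the timeline is not visible. That stands in part: nothing here shows that no rule exists anywhere. It does not remove the point, because the article itself sets two unranked primary outcomes against a power figure for one test of one of them.

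Four stronger readings are tempting but not supported.

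- **The plan prescribes six tests, any of which suffices.** The text says only that changes will be compared. The six-test error rate shows what the open wording would allow.
- **The familywise error is 26.5%.** That needs independence, which is implausible here, and an alpha that the article does not state.
- **The 3- and 12-month contrasts are contaminated.** The advice arm's request ends at four weeks, but no rate of later manual treatment is given. The approach is pragmatic, analysis is by intention to treat, and care outside the study is recorded for the cost analysis. Later contrasts may include such treatment; that is all.
- **The article contradicts itself on pain.** The remark "rendering pain a less than optimal primary outcome measure" explains why a global rating was chosen as well. It is a disclosed limitation and agrees with keeping pain as one of two primaries. It is still a reason not to let pain carry the claim alone.

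The duplicate secondary listing might be meant to cover other visits, but the article does not say so.

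**Conclusion.** The concern holds in this form: the visible text fixes two unranked primary outcomes without a primary visit or success rule, and the sample size allows for one test only. If all six comparisons were tested at 0.05 and any one counted, the familywise error would be about 11-25%. Fixing the visit but leaving both outcomes open would leave about 7-10%. Controlling the two outcomes by Bonferroni at one visit lowers power at 120 patients from 81% to about 72%.

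These figures rest on a two-sided alpha of 0.05, inferred because it reproduces the stated power, and on correlations of 0.3 to 0.9, which are assumed. The power figure itself comes from a 5-point scale in chronic patients, a difference that the article acknowledges.

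**What to change.** In a dated amendment, before any unblinded comparison:

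1. Name one primary outcome and one primary visit, and state alpha and sidedness. Improvement in chest pain is the natural outcome because it is the one powered. Week 4 is a reasonable visit because treatment and the advice arm's request both end then. The power calculation names no visit, so week 4 is a judgement; another single visit fixed in advance would also settle the matter.
2. Test worst pain at the same visit only if the primary result is significant. Treat the 3- and 12-month results as supportive.
3. Remove the two primary outcomes from the secondary list, or state which visits that listing covers.
4. State that the MANCOVA is supportive and gates nothing.

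This keeps the single-test basis for 81% power and adds no patients or visits. If both outcomes are to stay primary, with success on either, fix the visit, split alpha and restate power at about 72% for 120 patients.

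The cost is that pain and the long-term results lose primary status. Because the trial is already running and registered, the amendment needs a stated reason and a matching registry update.
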